#### Inflammatory measures

Serum blood samples are taken to measure inflammatory markers, such as cytokine levels (e.g., IL-6, Il-8), at baseline, on the day of vaccination, at the start and end of the test day, and at follow-up. A heparin blood sample is taken at baseline, on the day of vaccination, and at the start of the test day. This sample is used to stimulate blood cells with LPS in vitro in a 37 °C incubator for 6 h; the stimulated and control plasma samples are then centrifuged and stored at −80 °C. All inflammatory parameters are measured in batches, including complete follow-up samples of individual participants.

#### Endocrine measures

Saliva is taken to assess endocrine responses (e.g., cortisol, alpha-amylase) at the same time points as the serum blood samples and additionally after each stress task on the test day, 1 day after vaccination.

### Statistical analyses

#### Primary outcome

Effects of the psychological intervention on vitality are assessed in an analysis of variance with inclusion of covariates (ANCOVA) when appropriate. Vitality after the psychological intervention is used as dependent variable, and condition (experimental or control condition) is used as a between-subjects factor. Baseline measurement of vitality is used as a covariate.

#### Secondary outcomes

Inflammatory responses measured in blood at the screening, after the intervention (on the vaccination day), on the test day 1 day after vaccination, and at the follow-up session are assessed in multilevel models. The inflammatory responses are used as dependent variables, with group allocation, baseline measurements, and time serving as independent variables. Analyses for LPS-stimulated blood (measured at the screening, on the vaccination day, and the start of the test day) are conducted in a similar way.

Endocrine responses measured in saliva at screening, after the intervention (on the vaccination day), after each stress task 1 day after vaccination, and during follow-up are evaluated as dependent variables in a multilevel model, with group allocation, baseline measurement of the dependent variable, and time as independent variables. Analyses for heart rate and skin conductance are conducted in a similar way.

Demographic variables and self-reported measures are explored as possible predictors of the primary outcomes.

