### Procedures

Participants are recruited from the Leiden University student population via local digital or printed advertisements. Testing takes place at the Leiden University Medical Center in The Netherlands. After providing informed consent to the test leader, participants are first screened for potential physical and psychiatric conditions that might interfere with their safety or with the study protocol. Participants who meet the inclusion criteria (see below for details) are randomized to the experimental or the control condition. Participants in the experimental condition receive a psychological intervention for 6 weeks; participants in the control condition do not receive any intervention during this period. Subsequently, all participants are given a BCG vaccination to challenge the immune system in vivo. One day after vaccination, participants take part in a test day, on which they perform psychophysiological tasks. Four weeks after the test day, finally, a follow-up session is planned in order to evaluate the effects of the psychological intervention on health outcomes in the longer term. The schedule of activities in the study is presented in Table 1.

**Table 1 Tab1:** Schedule of study activities

		Study period				
Visit	Screening	Allocation	Intervention period	Vaccination day	Test day	Follow-up
Time point	Week 0	Week 4	Weeks 4–10	Week 10	Week 10	Week 14
Enrolment:						
Eligibility screen	X					
Informed consent	X					
Allocation		X				
Interventions:						
Intervention condition			X			
Control condition			X			
Assessments:						
Serum blood sample	X			X	X	X
Heparin blood sample	X			X	X	
Medical screening questionnaire	X					
MINI Psychiatric Interview	X					
IGRA test (interferon-gamma release assay)	X					
HIV test	X					
Vaccination				X		
Psychophysiological stress tasks					X	
Saliva samples	X			X	X	X
Heart rate, heart rate variability and skin conductance levels	X				X	X
Questionnaires	X			X	X	X

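### As worded, the secondary multilevel models use the pre-randomisation screening value as both outcome row and covariate, which dilutes the group effect by (T−1)/T

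*Protocol article*

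**What the plan says.** The Secondary outcomes section of the protocol article sets out three models and refers to them for a further group of measures.

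- **Serum inflammatory markers.** The responses are those "Inflammatory responses measured in blood at the screening, after the intervention (on the vaccination day), on the test day 1 day after vaccination", and at follow-up. The next sentence gives the model: "The inflammatory responses are used as dependent variables, with group allocation, baseline measurements, and time serving as independent variables".
- **LPS-stimulated blood.** It is handled likewise, with samples "measured at the screening, on the vaccination day, and the start of the test day".
- **Saliva.** "Endocrine responses measured in saliva at screening, after the intervention (on the vaccination day), after each stress task 1 day after vaccination", and at follow-up, are the dependent variables, "with group allocation, baseline measurement of the dependent variable, and time as independent variables".
- **Heart rate and skin conductance.** Only a cross-reference is given: "Analyses for heart rate and skin conductance are conducted in a similar way". No outcome rows are listed.

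No group-by-time term is named, and nothing limits the outcome rows to visits after randomisation.

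The Inflammatory measures section dates the serum samples "at baseline, on the day of vaccination, at the start and end of the test day, and at follow-up". Table 1 shows no sample between screening (week 0) and vaccination day (week 10), so baseline and screening are the same sample. Screening comes before allocation: "Participants who meet the inclusion criteria (see below for details) are randomized to the experimental or the control condition".

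**The concern.** Read plainly, the screening value stands on both sides of the model. As an outcome row it is predicted perfectly by itself. Because it precedes randomisation, it carries no information on the intervention. A single group coefficient that averages over all rows is then pulled towards zero by a row in which no effect can exist.

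These models carry the inflammatory and endocrine results and, by reference, the psychophysiological ones. An understated effect with an unremarkable p-value would be easy to miss, and the published estimates and intervals would be the ones carried into later studies or meta-analyses.

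**Working it through.** The article states no figure for these models, so there is none to reproduce. Its sample-size paragraph rests on self-reported outcomes and does not bear on this point.

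**Inputs from the article.** There are 30 participants per condition. Rows per person, one of them screening, are:
- LPS blood, T = 3;
- serum, T = 4 (T = 5 if the start and end of the test day are both modelled);
- saliva, T = 6 (screening, vaccination day, after each of three tasks, follow-up).

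**Assumed.** Complete data, unit variance, equal within-person correlation ρ, and a constant post-baseline effect δ. If the effect varies by visit, read δ as its average.

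**Step 1: dilution.** In a balanced random-intercept model with group, baseline and time, the group coefficient comes from the person means. Write the mean of person i over all rows as

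M_i = (1/T)·Y_i0 + ((T−1)/T)·P_i,

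where Y_i0 is the screening value and P_i the mean of the post-baseline rows. Regress M_i on group and Y_i0. The first term is absorbed wholly by the baseline coefficient, so the group coefficient is (T−1)/T times the one from regressing P_i on group and Y_i0.

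| Outcome | T | Factor | Understatement |
|---|---|---|---|
| LPS blood | 3 | 2/3 = 0.67 | 33% |
| Serum | 4 | 3/4 = 0.75 | 25% |
| Serum, both test-day samples | 5 | 4/5 = 0.80 | 20% |
| Saliva | 6 | 5/6 = 0.83 | 17% |

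The factor does not depend on ρ. Mixed-model fits to simulated data gave ratios of 0.667 (T = 3) and 0.750 (T = 4).

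**Step 2: standard error and test.** The residual of M_i is scaled by the same factor, so the standard error is too. The fitted ratios were 0.669 and 0.750. The t statistic is therefore practically unchanged. In simulation with T = 4, ρ = 0.5 and δ = 0.5, power was 84.5% and type I error 4.2% with or without the screening row.

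**Step 3: coverage of the true effect.** With m = T−1,

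SE_post = √{[ρ + (1−ρ)/m − ρ²] × 2/30}.

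The interval is centred on mδ/T and has standard error (m/T)·SE_post. It misses δ by s = δ/(m·SE_post) standard errors on average, so coverage is Φ(1.96 − s) − Φ(−1.96 − s). For ρ = 0.5 and δ = 0.5:

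| T | SE_post | s | Coverage |
|---|---|---|---|
| 3 | 0.183 | 1.37 | 72% |
| 4 | 0.167 | 1.00 | 83% |
| 6 | 0.153 | 0.65 | 90% |

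A check simulation (5,000 data sets) gave 72%, 83% and 90%. For ρ from 0.3 to 0.7 at δ = 0.5, the formula gives 64–75% (T = 3), 79–84% (T = 4) and 88–90% (T = 6). At δ = 0.3 and ρ = 0.5 it gives 87%, 91% and 93%. With screening as covariate only, coverage in the check was 94–95%.

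**Step 4: the alternative reading with group-by-time.** The group contrast at the last visit is not shrunk (simulated means 0.48–0.51 for a true 0.50). The screening row has no residual variation once it is its own covariate, however, and pooling it with the other rows makes the standard error too small. At ρ = 0.5 the model standard error was 0.193 against an empirical 0.227 (T = 3), and 0.202 against 0.222 (T = 4). Type I error was 9.1–10.3% with 3 rows and 6.0–7.4% with 4. The check simulation, using the normal critical value 1.96, gave 10–11% and about 8%. Without the screening row, type I error was 3.7–6.3%.

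**The case against.** **The wording may be loose.** The article condenses a fuller plan. For the inflammatory outcomes, one sentence lists when blood is drawn and the next assigns roles, and screening must appear in the list because it supplies the covariate. The primary analysis shows that the authors know how to use baseline as a covariate only. This is a fair possibility, and it is why the remedy is a clarification. It does not remove the point. The saliva sentence names the screening sample among the dependent variables and its baseline value among the predictors in one breath, and nothing elsewhere restricts the rows. This is a stated rule, not a detail left for later.

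**The interval is not falsely precise.** A reader might infer that the duplicated row deflates the residual variance and so makes the interval too narrow as well as shrinking the estimate. For the model as listed this is not so. The standard error matches the empirical spread, and coverage of the diluted quantity is about 95%. In one simulation (T = 4, ρ = 0.5) the within-person residual variance was 0.524 with the screening row and 0.501 without. The poor coverage in Step 3 is the dilution seen from another side. A standard error that is truly too small arises only under group-by-time, where there is no shrinkage. No single reading gives both harms.

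**Not every secondary outcome is equally hit.** Heart rate and skin conductance are covered only by cross-reference, with no rows listed, so no factor can be given for them. For saliva the loss is modest. A constant effect across a pre-challenge visit, the day after BCG and four weeks later is also unlikely, so the factor is best read as applying to the average effect. All of this stands.

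**Conclusion.** Wrong as written, for secondary outcomes only. With the terms as listed, the group coefficient understates the average post-baseline effect by 33% (LPS blood), 25% (serum; 20% with five samples) and 17% (saliva). These factors rest on complete, balanced data and a single group term. The coverage figures rest in addition on assumed effect sizes and correlations, and they approach 95% as the effect gets smaller.

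It would go too far to conclude that the tests of the listed model are invalid or that findings would change from significant to non-significant, because p-values, power and type I error are practically the same. If the analysts add group-by-time, the harm is a different one: mildly to clearly anti-conservative visit-specific tests, worst with three rows. The article does not settle which model is meant. The primary ANCOVA takes only the post-intervention value as outcome and is not affected.

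**What to change.** State in the Secondary outcomes section, for each outcome including heart rate and skin conductance, that the outcome rows are the post-randomisation visits only (vaccination day onward, where measured) and that the screening value enters solely as covariate. This matches the primary ANCOVA. Add group-by-time if visit-specific effects are wanted.

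Alternatively, keep screening as an outcome row, constrain the group means to be equal at that visit, and drop the baseline covariate. Choose one of the two and apply it throughout.

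The cost is one sentence of wording. No data, visits or participants are added, and the sample size is unaffected.

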#### Sample size calculation

The final power calculation was based on a study examining the effects of a stress management intervention on the level of psychological distress, using a comparable design [24]. Power analysis of this study indicated that 30 participants per condition would be sufficient to detect an adjusted effect size of *f* = 0.45 on psychological distress, with a power of 0.80, and an alpha level of 0.05. For the SVS, one representative study has found an effect size of *f* = 0.44 in change in vitality at post intervention in an uncontrolled study on a walking intervention including a motivational intervention [49]; an effect size of *f* = 0.40 was found in another representative study for the difference in change in vitality between an endurance intervention group and a control group at post intervention [50]. Also, with regard to the CIS-20, similar effect sizes have been reported for cognitive behavioral interventions in, among other populations, patients with rheumatoid arthritis [51]. Therefore, a total sample size of 60 participants was deemed sufficient to identify detectable and clinically relevant differences in the outcome parameters of the current study.

## Discussion

The present study evaluates whether self-reported and physiological health outcomes can be modulated by a psychological intervention directed at optimizing immune function. The intervention consists of guided e-health CBT in combination with health-related serious gaming elements and will be tested in healthy men. The study will contribute to the findings on the effects of psychological interventions on psychophysiological stress reactivity after an immunological challenge and provide further evidence on the link between psychological and immunological mechanisms [7].

A unique feature of this study is that we use a psychological intervention based on multiple strategies (e-health CBT and serious gaming) directed at optimizing immune function. The study is among the first to use a combination of guided e-health CBT and health-related serious gaming elements. Serious gaming can be a promising add-on to e-health CBT since this highly innovative tool can strengthen skills, attitudes, and knowledge about health in an entertaining manner. The results of the present study will, therefore, provide more insight into these psychological interventions directed at optimizing immune function and their potential effectiveness on health outcomes, both self-reported and physiological. Furthermore, the advantages of e-health CBT are that both participants and therapists can use and log on to the intervention at the time and place they prefer. Therefore, the intervention developed may be easier to use, more time efficient, and consequently less expensive than traditional face-to-face therapy. Complementing guided e-health CBT with health-related serious gaming elements seems to be a promising approach to optimize health outcomes, since multiple cognitive behavioral strategies are involved. If the combined intervention of guided e-health CBT and health-related serious gaming elements turns out to be effective in modulating self-reported and physiological health outcomes, the individual components of this psychological intervention can be investigated in further studies in order to gain more insight into the effectiveness of the different components.

In addition to an innovative psychological intervention, the study design incorporates validated immunological challenges in the form of in vivo and in vitro stimulation of immune responses. A previous study incorporated a hepatitis B vaccination to investigate the effects of an emotional disclosure intervention on immune reactivity [52]. The researchers found that participants who received the emotional disclosure intervention showed higher levels of antibodies in response to the hepatitis B vaccination than the group who did not receive any intervention. Live vaccines, such as the BCG vaccine, come closer than other vaccines to eliciting the same immune response as is observed after natural infection. Consequently, by including BCG vaccination as an immunological challenge, this study will provide more insight into the real-life effects of a psychological intervention on immune function and subsequently on the development of protection against infectious diseases. Besides BCG vaccination, LPS stimulation in vitro at baseline, before vaccination, and after vaccination provides more insight into the in vitro immune reactivity that occurs in response to a psychological intervention.

The study also incorporates psychophysiological tasks. This allows us to obtain more insight into the psychological intervention’s effects on stress reactivity. Previous studies have shown that various stressors can lead to different psychophysiological stress responses. More heightened endocrine responses and anticipatory stress appraisals were found after exposure to the TSST than after exposure to the CPT [53, 54], for example. By combining multiple psychophysiological and physiological stressors, more detailed information can be gathered about the stress response following an immune challenge. In addition, this study is one of few studies to evaluate the effects of a psychological intervention on health outcomes at follow-up [23, 24]: the study design incorporates a test session 4 weeks after the intervention. By implementing in vivo and in vitro immunological challenges and psychophysiological challenges in combination with a follow-up measurement, this study has the potential to advance scientific knowledge into the mechanisms underlying the relation between psychological and immunological factors.

In conclusion, the present study design is expected to provide valuable information about the role of psychological mechanisms in optimizing health outcomes in healthy men. It will help to unravel the underlying mechanisms of psychophysiological stress reactivity to immunological challenges and may ultimately contribute to the development of new health care strategies. If it turns out that this psychological intervention can modulate various health outcomes, it can be implemented in health care and may partially or fully replace medication use. This may mean that fewer people suffer from the side effects of medication use and may also lead to reductions in health care costs.

## Trial status

This trial is currently in the participant recruitment phase.

## Abbreviations

ANCOVA: Analyses of covariance
BCG: Bacillus Calmette-Guérin
CBT: Cognitive behavioral therapy
CIS-20: Checklist Individual Strength
CPT: Cold Pressor Test
DSM-5: Diagnostic and Statistical Manual of Mental Disorders, version 5
GCP: Good Clinical Practice
ICH: International Conference on Harmonization
LPS: Lipopolysaccharide
NTR: Nederlands Trial Register
PASAT: Paced Auditory Serial Addition Task
RCT: Randomized controlled trial
SPIRIT: Standard Protocol Items: Recommendations for Interventional Trials
SVS: Subjective Vitality Scale – State version
TB: Tuberculosis
TSST: Trier Social Stress Test
